# Home Telemonitoring of Arterial Hypertension With Antihypertensive Treatment Titration: Protocol for a Randomized Controlled Prospective Trial (HOROSCOPE Study)

**DOI:** 10.2196/26184

**Published:** 2022-03-01

**Keywords:** telemonitoring, arterial hypertension, primary care, ambulatory blood pressure monitoring, randomized controlled trial

## Abstract

**Background:**

Despite the availability of effective treatment, the control of hypertension remains insufficient. Telemonitoring in the management of hypertension would be an effective way to improve blood pressure control.

**Objective:**

The aim of our study will be to evaluate the effects of telemonitoring with antihypertensive treatment titration on blood pressure control in Tunisian patients with hypertension.

**Methods:**

Our trial will be a prospective, rater-blinded randomized controlled trial carried out with primary care physicians in the Sahel region of Tunisia. Patients will be eligible for enrollment if they are aged over 35 years, are newly diagnosed with hypertension, or are known to be poorly controlled on antihypertensive therapy. Participants will be randomly assigned in a 1:1 ratio to the telemonitoring arm or usual care arm. The telemonitoring arm will involve a weekly telephone call for the collection of the home blood pressure measurements, therapeutic education, and treatment compliance assessment as well as a monthly call for treatment titration and a side effect check. Randomization will be done via the use of an interactive web responsive system, and patients will be stratified by investigation center. Neither participants nor investigators will be masked to the group assignments. The primary outcome will be the change in mean 24-hour systolic blood pressure from baseline to the 6-month follow-up in the 2 groups. All randomized patients who attend the follow-up visit at 6 months and have no missing data for the primary outcome will be included in the analysis.

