### Sample Size

A sample size of 199 subjects per group is required for 80% power, assuming a mean difference in the reduction of SBP of at least 5 mm Hg between the two study groups and an SD of 15 mm Hg. Considering a patient dropout ratio of 15%, the study will need to recruit 230 subjects in each group.

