### Statistical Analysis

Categorical variables will be expressed as frequencies and percentages, while continuous variables will be expressed as means with SDs. An analysis of variance will be performed to compare the two study groups in terms of the primary end point. The normality of continuous data will be assessed with the Shapiro-Wilk test. Furthermore, we will use a general linear model for repeated measures to compare the marginal means of Gaussian quantitative dependent variables before and after the intervention (a Bonferroni test will be considered). A nonparametric test (the Friedman test) will be used for the comparison of non-Gaussian quantitative variables before and after intervention. The Cochran Q test will be performed to compare binary dependent variables before and after intervention. Subgroup analyses will be performed by age (<65 years and ≥65 years), sex, and the severity of hypertension. Differences between continuous variables will be evaluated with a 2-tailed Student *t* test or by its correction, as appropriate. The differences among the categorical variables will be evaluated with the Pearson chi-square test. All tests will be considered significant at the cutoff value of *P*<.05.

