Data will be collected via an electronic data capture system (Dacima Clinical Suite; Dacima Software Inc) that is compliant with international data security requirements (ie, those of the US Food and Drug Administration [FDA] Title 21 of the Code of Federal Regulation [CFR], part 11; Health Insurance Portability and Accountability Act [HIPAA]; International Council for Harmonisation of Technical Requirements for Pharmaceuticals for Human Use [ICH]; and General Data Protection Regulation [GDPR]). Dacima Clinical Suite is authorized by the local body of personal data protection. The electronic case report form will be used to perform quality checks on the data (checks on simple controls [eg, range check], eligibility criteria, and complex controls) to increase the accuracy of the data. Double data entry will not be scheduled, as data will be directly captured in the electronic data system. Investigators and research assistants will use monitoring data tools as an audit trail for tracking the data modification log, data queries, and electronic signatures. Research assistants will use source document verification tools to ensure the accuracy of the collected data. Automatic alerts will be implemented to notify the responsible investigator about any data or protocol violations.

Participants who do not have data on the primary outcome at the 6-month follow-up assessment will be labeled as those who are missing data for the primary outcome at this time point. A further sensitivity analysis will include participants with 1 missing measurement. The frequency (percentage) of losses to follow-up (defaulters and withdrawals) after 6 months will be reported by randomized group and compared between the two groups. The availability of the outcome data for the primary and secondary outcomes will be summarized for the two randomized groups. The mixed-effects model implicitly accounts for data missing at random; however, the missing data mechanism will be explored. A logistic regression model will be used to explore any associations between baseline characteristics and the availability of data on the primary outcome. Any changes to the assumptions made in the primary analysis (ie, data missing at random) will be considered in a sensitivity analysis.

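### The primary analysis is ANOVA on 6-month completers, yet its missing-data handling is credited to a mixed-effects model that is not among the planned methods

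*Protocol article*

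**What the plan says.** Four statements in the protocol article bear on this point.

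- Analysis set (Abstract, Methods): "All randomized patients who attend the follow-up visit at 6 months and have no missing data for the primary outcome will be included".
- Primary test (Statistical Analysis): "An analysis of variance will be performed to compare the two study groups in terms of the primary end point". The same paragraph adds, for comparisons before and after the intervention, "we will use a general linear model for repeated measures to compare the marginal means of Gaussian quantitative dependent variables", along with Friedman, Cochran Q, t and chi-square tests.
- Missing data (Statistical Analysis, last paragraph): "The mixed-effects model implicitly accounts for data missing at random; however, the missing data mechanism will be explored". This is the only mention of a mixed-effects model in the article.
- Sensitivity analyses (same paragraph): "A further sensitivity analysis will include participants with 1 missing measurement", and "Any changes to the assumptions made in the primary analysis (ie, data missing at random) will be considered in a sensitivity analysis". Losses are also to be compared by group, and a logistic regression is to relate baseline characteristics to availability of the primary outcome.

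Sample Size allows for the losses: "Considering a patient dropout ratio of 15%, the study will need to recruit 230 subjects in each group". Table 1 schedules ambulatory monitoring (ABPM) at day 29 and month 6 only. The section on clinic examinations makes an adequate ABPM recording a condition of randomisation.

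**The concern.** The analysis set is defined by something that happens after randomisation: attending at 6 months with usable data. The reassurance offered about missing data belongs to a different model from the one planned. A reader would conclude that the primary result is valid under missing at random, whereas ANOVA of change in completers needs a stronger condition.

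Arm-dependent loss is plausible here. Participants and investigators know the allocation. The telemonitoring arm has weekly and monthly calls and measures blood pressure at home on three days a week; the control arm has visits every 3 to 6 months and no calls. Strengths and Limitations acknowledges that measurement and questionnaire burden could lead to dropout. If loss depends on arm and on blood pressure response, the completer comparison no longer estimates the difference between the groups as randomised.

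**Working it through.** **1. The plan's own figures.** Inputs from Sample Size: difference 5 mm Hg, SD 15 mm Hg, 80% power, 199 per group, 15% dropout, 230 recruited per group. Two-sided 5% is assumed.

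- n per group = 2 × [15 × (1.960 + 0.842) / 5]² ≈ 141.3, so 142. The stated 199 does not reproduce at 80% power; it gives about 91%. That is a separate matter.
- Inflation for dropout: 199 / 0.85 = 234.1, so 235; 199 × 1.15 = 228.9, so 229. The stated 230 lies close to both.
- Patients excluded: 0.15 × 230 = 34.5 per arm. Completers: 230 × 0.85 = 195.5 per arm, with power of about 91% at 195. The issue is therefore bias, not loss of power.

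**2. Does any planned method supply the claimed protection?**

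- ANOVA uses only patients with the outcome.
- The general linear model for repeated measures is the nearest candidate. In its classical form it drops incomplete cases, and it is described for before/after comparison.
- A true mixed model on ABPM would have one pre-randomisation and one post-randomisation value. A patient without the second contributes little beyond baseline, and nothing if the model is fitted to completers only.

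**3. The analysis with one missing measurement.** The baseline recording is required before randomisation. For a two-point change in 24-hour SBP, the single missing value can then only be the 6-month one. The article does not define the term or say how such patients would enter.

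**4. Size of the bias.** Let p be the fraction missing in an arm and g the amount by which missing patients' SBP reduction falls short of completers'. The mean reduction over all randomised patients is the completer mean minus p × g. Hence, for telemonitoring (T) and control (C):

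bias of the completer difference = p_T × g_T − p_C × g_C

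The documents give only 15% overall; the splits and gaps below are assumptions.

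| p_T | p_C | g_T | g_C | Bias (mm Hg) |
|---|---|---|---|---|
| 0.15 | 0.15 | 10 | 10 | 0 |
| 0.20 | 0.10 | 5 | 5 | 0.5 |
| 0.20 | 0.10 | 10 | 10 | 1.0 |
| 0.15 | 0.15 | 10 | 5 | 0.75 |

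A bias of 0.5 to 1.0 mm Hg is 10% to 20% of the 5 mm Hg target. The standard error of the difference with 195 per arm is 15 × √(2/195) ≈ 1.5 mm Hg. The sign reverses if control loses more patients.

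**5. Simulation under missing at random.** There was no true effect, 230 per arm, SD of change 15 and about 15% dropout, with 2000 runs per setting. Assumptions: baseline to 6-month correlation of 0.3 to 0.7, and a dropout log-odds slope of 1 per baseline SD.

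| Dropout | Bias, ANOVA of change (mm Hg) | Type I error |
|---|---|---|
| Completely at random | about 0 | about 5% |
| Depends on baseline in one arm | 0.8 to 1.2 | 7% to 11% |
| Depends on baseline, opposite directions by arm | 1.6 to 2.4 | 18% to 36% |

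A baseline-adjusted model on the same completers had bias of about 0 and type I error of about 4% to 6% throughout. The planned ANOVA is thus not protected under missing at random, even when dropout depends on baseline alone.

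**The case against.** The strongest reply is that this is loose labelling. The mixed-effects model may mean the repeated-measures general linear model, the completer restriction appears only in the Abstract, and Ethics and Dissemination refers to a statistical analysis plan that is not shown and may settle the matter. The labelling explanation is possible. It does not help, because the classical general linear model also needs complete cases. Whatever the analysis plan says, the article's own statements still conflict.

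Three stronger readings are tempting, and the documents do not support them.

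- *That nothing planned addresses the missing data.* The missing-data paragraph promises a sensitivity analysis to departures from missing at random, a comparison of losses by group and a regression on availability. The last two only diagnose, and the first has no named method, but missing data are not ignored.
- *That the analysis with one missing measurement cannot be done.* It is undefined, not impossible: the 6-month value could be imputed.
- *That the randomised comparison is certain to be broken.* The article says that burden could cause dropout; it predicts no imbalance. The bias figures rest on assumed splits and gaps, and zero is within the possible range.

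Two further objections stand. The 6-month ABPM is already scheduled for every patient, so no new collection rule is needed. Baseline adjustment alone sufficed in every simulated setting; imputation adds protection only where later data carry information about the missing outcome, and mainly for patients who attended month 3.

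**Conclusion.** The concern holds. As described, the primary analysis is a completer ANOVA without the missing-at-random property that the article claims for it. About 34 patients per arm would be excluded at the planned dropout. The consequence ranges from no bias, with equal dropout and equal gaps, to about 0.5 to 1.0 mm Hg with 20% versus 10% dropout and a gap of 5 to 10 mm Hg. The top of that range is about two-thirds of a standard error (1.0 / 1.5).

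These figures assume that the primary outcome is the mean change in 24-hour SBP given in the Abstract. Primary Outcome instead defines a percentage of patients reaching a 10 mm Hg change. The conflict over the analysis set is the same for either outcome, but the size in mm Hg applies only to the first. Because the primary comparison is affected and the remedy uses data already scheduled, this should be corrected before analysis.

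**What to change.** 1. Settle first whether the primary outcome is the mean change or the percentage of patients, then make the Abstract and both parts of Statistical Analysis agree.
2. Define the primary analysis set as all randomised patients in their allocated arm.
3. Impute missing 6-month 24-hour SBP by multiple imputation within arm, using day-29 24-hour SBP, clinic blood pressure at inclusion, day 29, month 3 and (if available) month 6, compliance, age, sex and centre. Fit a baseline-adjusted model, and derive any responder outcome from the imputed values.
4. Keep the completer analysis as a sensitivity analysis.
5. Specify the promised analysis of departures from missing at random as delta-adjusted, with the shift varied separately by arm.
6. Define or replace the analysis with one missing measurement, and delete the mixed-model sentence.

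The cost is wording and some added analysis work; no new data are needed. The downside is reliance on the imputation model, which the completer and delta-adjusted analyses help to test.

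### The primary analysis is an ANOVA of completers, so it lacks the missing-at-random cover that the protocol credits to a mixed-effects model it never specifies

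*Protocol article*

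**What the plan says.** Three statements bear on the primary analysis.

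- **Who is analysed** (abstract, Methods): randomized "patients who attend the follow-up visit at 6 months and have no missing data for the primary outcome will be included in the analysis".
- **How the arms are compared** (Statistical Analysis): "An analysis of variance will be performed to compare the two study groups in terms of the primary end point". The only repeated-measures method named for normally distributed data is for before-and-after comparison: "we will use a general linear model for repeated measures to compare the marginal means of Gaussian quantitative dependent variables". The rest are the Friedman, Cochran Q, t and chi-square tests.
- **What is assumed about missing data** (Statistical Analysis, later): "The mixed-effects model implicitly accounts for data missing at random; however, the missing data mechanism will be explored". The section closes: "Any changes to the assumptions made in the primary analysis (ie, data missing at random) will be considered in a sensitivity analysis".

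The section also plans to report and compare losses to follow-up by arm, to regress outcome availability on baseline characteristics, and this: "A further sensitivity analysis will include participants with 1 missing measurement". It names no method for either sensitivity analysis.

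**The concern.** The missing-data text refers to a mixed-effects model as if it had been introduced, but it appears nowhere else. The analysis set and method that are stated give a complete-case comparison. A reader of the final report would be told that the primary result holds under missing at random, when the analysis performed needs a different condition: that dropout does not shift the observed change differently in the two arms.

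That condition could fail in this trial. Sample Size allows for 15% dropout. Study Design says that neither participants nor investigators are masked. Only the telemonitoring arm has home readings and weekly calls (Control Group and Intervention Group). Strengths and Limitations names measurement burden as a possible cause of dropout.

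**Working it through.** **1. Do the statements fit together?** The abstract's set contains no one without the 6-month outcome. A mixed model gains its missing-at-random property by keeping patients whose outcomes are partly missing. On this set every primary outcome is present, so the model has nothing to account for. Either the analysis set or the missing-data sentence must change.

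**2. How many patients?** Sample Size: 230 per arm, 15% dropout. 2 × 230 = 460; 0.15 × 460 = 69 expected without the outcome and 391 with it. (The stated 199 per arm does not reproduce at 80% power: 5 mm Hg and SD 15 at two-sided 0.05 need 142. Nothing below depends on that.)

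**3. When is ANOVA of completers biased?** In each arm, the error in the completers' mean change equals (proportion missing) × (stayers' mean change minus leavers' mean change). The treatment estimate is off by the difference between the two arms' errors. If leavers differ from stayers by an assumed 10 mm Hg in one arm only, the error is 0.15 × 10 = 1.5 mm Hg. If both arms have the same rate and the same gap, it is 0.

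**4. How large under missing at random?**

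*From the protocol:* difference 5 mm Hg, SD of change 15, 15% missing, applied to each arm.

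*Assumed:* SD 15 at day 29 and at month 6 with correlation 0.5 (so the SD of change is √(225 + 225 − 2 × 0.5 × 225) = 15); log-odds of leaving rise by 1 per SD of the driving variable. By numerical integration, stayers then sit 0.133 SD below the arm mean on that variable.

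Error in the arm = (correlation of driver with change) × 15 × (−0.133).

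- *Driver is day-29 SBP.* Correlation with change = (0.5 × 225 − 225)/(15 × 15) = −0.5. Error = −0.5 × 15 × −0.133 = +0.99. In the telemonitoring arm only, the estimate is −5 + 0.99 = −4.01. With opposite directions in the two arms it is about −5 + 1.99 = −3.01.
- *Driver is 3-month office SBP*, assumed to correlate 0.6 with month-6 and 0.5 with day-29 24-hour SBP. Correlation with change = 0.6 − 0.5 = 0.1. Error = −0.20, so −5.20 in one arm; about −5.40 with opposite directions. With correlations 0.65 and 0.42 the error is −0.46, so −5.46.

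Simulations agree:

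| Dropout depends on | ANOVA of change, completers | Baseline-adjusted, completers | Also using 3-month SBP, all patients |
|---|---|---|---|
| Nothing | −5.02 | −5.02 | −5.02 |
| Day-29 SBP, telemonitoring arm | −3.97, −4.05 | −4.99, −5.04 | −5.00, −5.03 |
| Day-29 SBP, opposite by arm | −2.93 | −4.95 | −4.98 |
| 3-month SBP, telemonitoring arm | −5.20, −5.48 | −5.71, −5.87 | −5.01, −4.96 |
| 3-month SBP, opposite by arm | −5.37 | −6.39 | −4.96 |

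Two values in a cell come from two separate simulations. At half the dependence (log-odds 0.5 per SD) the day-29 errors fall to 0.54 and 1.09 mm Hg.

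**5. Would adding a mixed model of 24-hour SBP be enough?** Table 1 schedules ambulatory monitoring only at day 29 and month 6. A patient without the month-6 value contributes only a baseline, so such a model gains little over baseline adjustment of completers. The table shows that this fails when leaving depends on 3-month pressure.

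**The case against.** - **The analysis plan may supply the model.** Detail may properly be left to it. But the protocol already states the set, the method and the assumption, and these conflict. A plan that follows one statement breaks another.
- **The repeated-measures general linear model may be the one meant.** Possibly. That it drops incomplete patients is its usual form, not something the document says. But it is assigned to before-and-after means, and the abstract's set removes incomplete patients anyway.
- **Sensitivity analyses are planned.** This stands against a stronger reading that a reader might infer, that the protocol makes no provision for missing data. It does: losses are compared by arm, availability is modelled, and two sensitivity analyses are mentioned. None changes the primary estimate, and the one on departures from missing at random is only to be considered.
- **Bias is not established.** Correct. A reader might infer that completer ANOVA is valid only if leaving is unrelated to change in each arm, or that the result will be biased. Neither follows: an equal shift in both arms cancels. Nor does the protocol predict dropout from burden; it says that this could happen.
- **The bias sizes rest on invented inputs.** They do. The correlations, the strength of dependence and the 10 mm Hg gap are assumptions. Recovery of about −5.0 in the last column is built in, because dropout was simulated from the variables that the method uses. No missing-not-at-random case was simulated.

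**Conclusion.** The contradiction stands on the text alone: the primary analysis as stated does not have the missing-at-random property claimed for it. The possible cost is bias; about 195 completers per arm still give some 91% power at the stated difference and SD. Under the assumptions shown, the error runs from about 0.2 to 2 mm Hg of the 5 mm Hg target, towards or away from no effect, and is zero if dropout is completely random or acts equally in both arms. These figures illustrate what is possible; they do not predict this trial's bias. This should be fixed; the documents do not show that the primary result must be wrong.

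**What to change.** 1. Settle the primary outcome first. The abstract says "The primary outcome will be the change in mean 24-hour systolic blood pressure from baseline to the 6-month follow-up in the 2 groups", while Outcomes defines a percentage of patients reaching a 10 mm Hg change. A mean-change ANOVA suits only the former.
2. Replace the abstract's restriction with all randomized patients, analysed in their assigned arm.
3. Name one primary analysis valid under missing at random that uses day-29 24-hour SBP, 3-month office SBP where available, and centre. Either a joint mixed model or multiple imputation by arm would serve. Patients who leave before month 3 lack the 3-month value, so imputation must cover it too.
4. Reword the mixed-effects sentence to match the method chosen; multiple imputation would not make it true as written.
5. Keep the completer ANOVA as a sensitivity analysis, and replace the promise to consider changed assumptions with a delta-adjusted analysis whose range is fixed in advance.

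The pressures are already scheduled in Table 1, and centre is the stratification factor. The cost is wording, more programming, and open reliance on missing at random, which the data cannot confirm; hence step 5.
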